### Safety aspects and medical complications

Safety parameters will comprise newly occurring mental diagnoses and all serious adverse events that are reported during and up to six months after treatment.

The recording of adverse events will be restricted to psychological conditions. Formally, they are defined as any disorder classified by the International Classification of Diseases F00 - F99. A serious adverse event (SAE) is an adverse event that may occur at any time of the treatment phase or up to 6 months after end of treatment: results in death; is life-threatening; requires subject hospitalization or prolongation of existing hospitalization; results in persistent or significant disability/incapacity; is a congenital anomaly/birth defect.

Any SAE (according to the study specific definition) reported by the subject or detected by the local investigator will be collected during the trial and must be documented in case report forms. ICD-10 will be used by the local investigator to code the event. The clinical course of the SAE will be followed until it has changed to a stable condition or until end of follow-up phase, whatever comes first. In case of SAEs the Ethics Committee will be informed within 24 hours after the SAE becomes known.

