### Participants

Members of the oncological teams report eligible consecutive patients to trained research assistants. Following detailed information those who provide written consent with study participation are entered into the study and fill out the screening questionnaire. Patients are required to fulfill the test criteria on the Hospital Anxiety and Depression Scale (HADS, depression score ≥8) and a diagnosis of a depressive disorder by the Structured Clinical Interview for DSM IV Disorders (SCID-I). Patients are randomized to the intervention or control group only if a diagnosis of a depressive disorder is made based on the aforementioned criteria. Inclusion and exclusion criteria are listed in Table
1.

**Table 1 T1:** Inclusion and exclusion criteria

*Inclusion criteria:*	· Diagnosis of breast cancer
	· Curative treatment
	· German language
	· Age 18-70
	· Depression score (HADS ≥ 8)
	· Depressive disorder according to SCID-I (ICD-10 diagnoses: depressive episode F32.-, recurrent depressive episode F33.-; Dysthymia F34.1, adjustment disorder F43.21)
	· Written consent with study participation
*Exclusion criteria:*	· Severe medical conditions (metastases, cognitive impairments) · Severe psychiatric disorders (psychotic disorder, risk of self-harm /suicide, acute substance related disorder, personality disorders except for cluster C, organic mental disorder) · Concurrent psychotherapeutic treatment

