### Outcome

Remission of depression is defined by reduction of the HADS depression-score (at least by 2 points) and remission of depression (SCID-I-diagnosis) at treatment termination.

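### Non-serious worsening of the entry depression is not a listed safety parameter, and the yes/no depression analyses do not separate it from no change or dropout

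*Protocol article*

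**What the plan says.** The section Safety aspects and medical complications sets the safety parameters: "Safety parameters will comprise newly occurring mental diagnoses and all serious adverse events". The window runs through treatment and for six months afterwards. On scope it says "The recording of adverse events will be restricted to psychological conditions", and on definition "Formally, they are defined as any disorder classified by the International Classification of Diseases F00 - F99". An adverse event is serious if it is fatal or life-threatening, involves a congenital anomaly, or meets one of these criteria: "requires subject hospitalization or prolongation of existing hospitalization; results in persistent or significant disability/incapacity". The section does not mention worsening of a disorder that was present at entry.

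Under Participants, "Patients are randomized to the intervention or control group only if a diagnosis of a depressive disorder is made". Table 1 lists what qualifies: "Depressive disorder according to SCID-I (ICD-10 diagnoses: depressive episode F32.-, recurrent depressive episode F33.-; Dysthymia F34.1, adjustment disorder F43.21".

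Under Outcome, "Remission of depression is defined by reduction of the HADS depression-score (at least by 2 points", together with remission of the SCID-I diagnosis at treatment termination. Statistical analyses adds that dropouts are non-remitters, that the two components are analysed separately by the same logistic model, and that remission at the end of follow-up is handled in the same way.

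**The concern.** The safety list looks for new diagnoses in a population selected for already having one. For these patients the most direct non-serious harm is that the depression they came with gets worse. That harm is not on the list unless it becomes serious or changes the diagnosis. Whether it changes the diagnosis may depend on the entry label. A move from adjustment disorder to a depressive episode plausibly counts as new. A depressive episode that becomes more severe may not, because the article does not say at what level of coding newness is judged.

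The efficacy analyses do not fill the gap, for a reason of their own: they are dichotomies of improvement. If only the described parameters were reported, either arm could appear free of non-serious harm while some of its patients had deteriorated. The trial would also be silent on whether STPP protects against worsening.

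**Working it through.** The plan gives no figure on deterioration to reproduce. The check is a reading of the definitions, with arithmetic only for the size of the groups.

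**1. Which worsening do the safety parameters capture?** Take a patient randomized with a depressive episode (F32.-).

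| Course | Listed safety parameter? |
|---|---|
| Worse; fatal, life-threatening, disabling, or with hospitalization | Yes, as an SAE |
| Worse, with a diagnosis not present at entry | Yes, as a newly occurring diagnosis |
| Worse within the same diagnosis, no seriousness criterion | No |

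The third row is the gap. All four entry diagnoses (F32, F33, F34.1, F43.21) lie inside F00–F99. The adverse event definition therefore covers these disorders by code, but gives no rule for one that is already present.

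**2. Do the depression analyses recover it?** Three are described:

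- the composite (HADS depression score down by at least 2 points and SCID remission);
- the HADS component alone, improved by at least 2 points or not;
- the SCID component alone, remitted or not.

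A patient whose HADS depression score rises by 5 points, one who is unchanged and one who improves by 1 point all fail the composite and the HADS component. A dropout is placed with them in the ITT analysis.

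**3. Illustration that the primary result does not react to deterioration.** Take the planned remission rates (25% TAU, 50% STPP) in 90 per arm, with two-sided alpha 0.05 (assumed; the article does not state it). Non-remission is 75% in TAU and 50% in STPP. Split it under three assumed worsening rates:

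| Worsened TAU / STPP (assumed) | Non-remitters not worsened, TAU / STPP | Power of the primary comparison (chi-square) |
|---|---|---|
| 0% / 0% | 75% / 50% | 0.94 |
| 5% / 15% | 70% / 35% | 0.94 |
| 10% / 30% | 65% / 20% | 0.94 |

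The primary analysis is the same in each row, even where three times as many STPP as TAU patients deteriorate.

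**4. How many patients would a deterioration count rest on?** Inputs: 90 per arm (Study design) and expected dropout of 20% in STPP and 30% in TAU (Sample size calculation).

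- STPP: 90 × (1 − 0.20) = 72 assessed.
- TAU: 90 × (1 − 0.30) = 63 assessed.

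**5. What could that comparison detect?** The worsening rates here are assumptions. Let p̄ be the pooled rate. Power = Φ[(|p1 − p2| − 1.96·SE0)/SE1], with SE0 = √[p̄(1 − p̄)(1/72 + 1/63)] and SE1 = √[p1(1 − p1)/72 + p2(1 − p2)/63].

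- 5% STPP against 10% TAU: p̄ = (3.6 + 6.3)/135 = 0.0733, SE0 = 0.0450, SE1 = 0.0457. Power = Φ[(0.05 − 0.0881)/0.0457] = Φ(−0.83), about 0.20.
- 5% STPP against 15% TAU: p̄ = (3.6 + 9.45)/135 = 0.0967, SE0 = 0.0510, SE1 = 0.0518. Power = Φ[(0.10 − 0.0999)/0.0518] = Φ(0.00), about 0.50.

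The count should be read through its confidence interval, not as a test.

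**The case against.** **Worsening is not wholly excluded.** A reader might infer that worsening of depression is never a safety outcome here. The text does not support that: serious worsening is an SAE, with no exemption for the entry disorder, and a changed F-diagnosis can count as new. This objection stands and confines the point to non-serious worsening without a new diagnosis.

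**The article is a condensed text.** Coding rules for pre-existing conditions commonly sit in the full protocol, which is not shown. For the coding level this is fair. It does not dispose of the point, because the article states what the safety parameters will comprise, and that list fits the population badly.

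**Any remission endpoint merges worse with unchanged.** True, and the Discussion defends remission as clinically relevant. The merging is a property of the endpoint and does not follow from the safety wording. The two facts stand side by side and matter together only for what can be said about harm.

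**Other outcomes would move.** A reader might infer that worsened patients disappear from every table. That is too strong. The abstract names reduction of the HADS depression score as a primary outcome measure, and the quality-of-life questionnaires, which include emotional functioning, are analysed by ANCOVA. Deterioration would pull those means down. But the described HADS analysis is only the 2-point dichotomy, and a mean does not show how many patients got worse.

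**A count of missed patients is tempting.** Any such number needs a worsening rate that the documents do not give. It would also have to assume that no worsened patient becomes an SAE, changes diagnosis or drops out. None should be claimed.

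**Conclusion.** The point holds in a limited form. Worsening of the qualifying depression that meets no seriousness criterion and brings no new diagnosis is not among the listed safety parameters. No described depression analysis separates it from no change, and the ITT analyses also place dropouts with it.

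The validity of the primary test and its sample size are not touched. What is affected is the completeness of any statement about harm, in either arm. The size is unknown. This rests on reading the safety parameters as a closed list, which is how the sentence is written; a full protocol that adds worsening to the list would settle that half. It is a worthwhile, inexpensive improvement, not a contradiction or a miscalculation.

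**What to change.** In Safety aspects and medical complications:

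1. Add deterioration of depression as a safety parameter at 6 and 12 months. Define it as a HADS depression score at least 2 points above baseline, which mirrors the trial's own improvement threshold.
2. Report by arm the number and percentage among assessed patients, the risk difference with 95% confidence interval, and the number not assessed. Alongside, report the change in HADS depression score.
3. State that worsening of a pre-existing F-diagnosis counts as an adverse event.
4. Keep the parameter on newly occurring mental diagnoses unchanged. Narrowing it to non-depressive diagnoses would remove events that it can capture now, such as a move from adjustment disorder to a depressive episode.

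The HADS count and score change come to one additional table, with no new visit, assessor or instrument; item 3 adds some adverse event recording. The limits should be stated with the table. HADS is completed by patients who know their treatment; only the assessors are blind. Some 2-point rises will be measurement noise, and with unblinded self-report and unequal dropout that noise need not be equal between arms. Patients who leave because they got worse remain uncounted, which is why the number not assessed belongs in the table. The comparison is descriptive, with low power.

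### Deaths without an F-coded cause are outside the safety data, and capture of suicide, suicide attempts and self-harm depends on how the local investigator codes them

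*Protocol article*

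**What the plan says.** All the rules are in the *Safety aspects and medical complications* section of the Protocol article.

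- Scope: "The recording of adverse events will be restricted to psychological conditions".
- Formal definition of an adverse event: "Formally, they are defined as any disorder classified by the International Classification of Diseases F00 - F99".
- An SAE is a kind of adverse event: "A serious adverse event (SAE) is an adverse event that may occur at any time of the treatment phase or up to 6 months" after treatment ends. The seriousness criteria include "results in death; is life-threatening; requires subject hospitalization or prolongation of existing hospitalization".
- Collection follows that definition: "Any SAE (according to the study specific definition) reported by the subject or detected by the local investigator will be collected during the trial". The local investigator codes the event in ICD-10, and the Ethics Committee is told of SAEs within 24 hours.
- What is reported: "Safety parameters will comprise newly occurring mental diagnoses and all serious adverse events that are reported during and up to six months after treatment".

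Elsewhere the article shows that the hazard is recognised. Table 1 (*Participants*) lists "risk of self-harm /suicide" among the exclusion criteria, and the *Intervention* section names suicidality among the topics that the therapy addresses. No section gives a separate rule for recording deaths from any cause, suicide attempts or self-harm.

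**The concern.** The definition works well for its apparent purpose, which is to keep frequent somatic events of cancer treatment out of the safety data. But it sorts events by whether they are mental disorders, and the gravest events in a depression trial are not disorders. A death is an outcome, and a suicide attempt or self-harm is an act. If such an event enters the data only when someone links it to a disorder code, two centers could treat the same event differently. A death that nobody linked to a mental disorder would not be there to be reviewed. Any statement about harm, overall or by arm, would then rest on data whose completeness is unknown for the events that matter most.

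**Working it through.** No figure in the plan is at issue, so the check follows the definitions in order and applies them to each type of event.

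**The chain**

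1. Adverse event = a disorder in F00-F99.
2. SAE = an adverse event from step 1 that meets a seriousness criterion.
3. Collected and notified = SAEs from step 2. The safety-parameter sentence speaks of all SAEs, but the collection sentence ties the term back to the study-specific definition, so it is no wider.

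**Applied to events**

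| Event | Adverse event? | SAE? | Where it appears |
|---|---|---|---|
| Depressive episode leading to hospital admission | Yes | Yes | Safety data |
| Suicide or serious attempt, coded as the fatal, life-threatening or hospitalised course of a depressive disorder | Yes | Yes | Safety data |
| The same event, recorded as an act without a disorder code | No | No | No rule captures it |
| Self-harm that meets no seriousness criterion | Only if a disorder is coded | No | A safety parameter only if there is a new mental diagnosis |
| Death with no F-coded cause | No | No | Not in the safety data |

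For the last row, the only trace that the article provides is in the efficacy analysis. *Statistical analyses* counts dropouts as non-remitters, and deaths are not distinguished there.

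Rows 2 and 3 can be the same event. What separates them is the investigator's coding, for which the article gives no instruction. The argument does not depend on where ICD-10 places self-harm codes, which the document does not say. It is enough that the definition requires a disorder.

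**New versus existing disorder**

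Table 1 requires an F32, F33, F34.1 or F43.21 diagnosis at entry, so every randomised patient already has a disorder inside F00-F99. The adverse event definition covers any such disorder, while the safety parameters cover newly occurring diagnoses. Non-serious worsening of the entry depression is not a new diagnosis, so it is not clearly counted as a safety event.

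**Window**

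The Abstract puts treatment termination at 6 months and follow-up at 12 months. Read on that calendar, the safety window ends at 6 + 6 = 12 months in both arms. Read from each patient's own end of treatment at month m, it ends at m + 6, which equals 12 only if m = 6, and TAU has no individual end of treatment to count from. The section does not say which reading applies.

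**Scale**

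The article gives no rate of death or self-harm. With 90 patients planned per arm, one event is 1/90 = 1.1% of an arm. This shows only how much a single missed event moves a proportion; it is not an estimate of how many would be missed.

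**The case against.** The strongest reply has four parts.

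- *The seriousness criteria already cover these events.* Every patient has an F-coded disorder to which a suicide or serious attempt can be attributed, and death, threat to life and hospitalisation are all listed. This stands. A reader might infer that suicide and self-harm can never be captured; the document does not support that. What remains is that attribution is permitted but not required, and that deaths without an F-coded cause stay outside.
- *The SAE list is consistent with the definition.* A reader might see a contradiction, because the list includes death and congenital anomaly while adverse events are mental disorders. There is none. The list filters events that already qualify, and the congenital-anomaly item is standard wording that an F00-F99 event would hardly meet.
- *Ascertainment need not be unequal.* A reader might set up to 25 therapy sessions in the STPP arm against two post-baseline assessments in TAU and take this as the size of a detection bias. It is not a measure of that. The named sources are the patient and the local investigator, and the private-practice therapists are not named as reporters. The article also plans blinded assessment in both arms and documentation of health care use. Some imbalance in spontaneous reports remains possible, but the document gives no size for it.
- *The restriction is deliberate, and this is a condensed article.* Patients are in active chemotherapy or radiotherapy, so leaving out somatic events is reasonable. No safety hypothesis is stated. HADS and SCID-I measure worsening depression as outcome data. The full protocol may hold further rules on deaths. These points limit the weight of the finding. They do not remove it, because the article states a formal definition and that definition excludes the deaths described.

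**Conclusion.** The point holds in a limited form. As defined, the safety data exclude deaths without an F-coded cause. Capture of suicide, suicide attempts and self-harm is not assured, because it depends on whether the local investigator codes the event as the course of an F-coded disorder. The document does not support saying that these events are always missed, or that one arm's count is biased by a known amount.

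The effect on the trial's safety results cannot be quantified from the document. The primary efficacy analysis is unaffected. The conclusion assumes that the formal definition is applied as written and that the full protocol has no separate rule for recording deaths and self-harm. If such a rule exists, only the wording of the safety section needs correcting. This is an inexpensive improvement worth making.

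**What to change.** Amend the *Safety aspects and medical complications* section as follows.

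1. Keep the restriction to F00-F99 for other somatic events.
2. Record as safety events, regardless of ICD chapter, every death from any cause and every suicide attempt or self-harm event, together with new or worsened F00-F99 disorders.
3. State the window as randomisation to the 12-month assessment in both arms.
4. Base any between-arm comparison on events asked about in the same way at the planned 6- and 12-month assessments, which blinded assessors already conduct. List spontaneously reported events separately.

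One limit should be stated with the results: interviews reach only patients who attend. If the dropout assumed in *Sample size calculation* (20% STPP, 30% TAU) applied to 90 per arm, 90 × 0.80 = 72 and 90 × 0.70 = 63 patients would be assessed. Denominators should therefore be given by arm, and deaths among non-attenders must be sought from other sources.

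The cost is a short amendment, a few questions at visits already planned, and a little more reporting.

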**Methods/design:**

Eligible breast cancer patients with comorbid depression are assigned to short-term psychodynamic psychotherapy (up to 20 + 5 sessions) or to treatment as usual (augmented by recommendation for counseling center and physician information). We plan to recruit a total of 180 patients (90 per arm) in two centers. Assessments are conducted pretreatment, after 6 (treatment termination) and 12 months (follow-up). The primary outcome measures are reduction of the depression score in the Hospital Anxiety and Depression Scale and remission of depression as assessed by means of the Structured Clinical Interview for DSM IV Disorders by independent, blinded assessors at treatment termination. Secondary outcomes refer to quality of life.

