**Figure 1 F1:**
[figure not shown]
**Study design and patient recruitment (N = projected numbers).** Notes: a) Questionnaires filled out by the patients; b) Structured Clinical Interview for DSM-IV applied by trained interviewers; c) HADS score for depression ≥ 8 & SCID-I diagnosis estimated in 20% of the cases (N = 240 eligible patients) of whom 75% are expected to be consent with randomization; d) Expected completer 80%, e) Expected completer 70%.

We plan to recruit N = 90 participants per group. To ensure adequate randomization stratified for the center, the random assignment to STPP or TAU was performed separately by research staff from the responsible center (not engaged in the project) using a computer-generated
[25] number series of random length (contained within closed, opaque envelopes.).

STPP entails five pre-treatment and up to 20 therapeutic sessions over a period of six months. In each center a close collaboration was established with about 10 psychodynamic psychotherapists in private practice who were trained according to the manual and supervised on a regular basis. Intensive training (at least 2 x 2 hours) is performed in a group format by the respective local study center prior to entering the first patient. Supervision is performed on a monthly basis (3 hours) in the group. In order to assure adherence to the manual, it is recommended that therapists present patients in supervision three times (initial formulation of CCRT based on relationship episode interview, middle and termination phase of treatment).

Patients randomized to the TAU condition are not offered STPP, but obtain written information on local cancer counseling centers and get written information on psychodiagnostic findings to their general practitioner who may then initiate antidepressant treatment (‘as usual’). Utilization of medical, psychotherapeutic and psychopharmacological treatment is documented throughout the study.

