### Sample size calculation

While planning this study no meaningful published data on remission rates for STPP vs. TAU for the treatment of depression in breast cancer were available. For STPP of depression remission rates between 45% and 70% at post-therapy assessment were published
[26], while remission rates in primary-care settings (comparable to TAU) ranged between 20% and about 50% (6 months)
[27-29]. For patients with complex medical illness like cancer and co-morbid depressive disorders we expect lower remission rates for TAU and also for STPP. For this highly burdened population we pragmatically expected a spontaneous remission rate of 25% for TAU and 50% for STPP in our sample size calculation.

In order to identify group differences of 25% (25% remission in TAU vs. 50% in STPP) as based on χ2-Test (two-tailed) and a power of 0.80 a total sample of N = 156 is required, taking into account a slightly higher dropout rate of 30% in the TAU group vs. a 20% in STPP.

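### SAE capture depends on patient report or investigator detection, while trial contact during treatment is very unequal, so a difference in SAE counts between arms could not be cleanly attributed to harm

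*Protocol article*

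**What the plan says.** All references are to the protocol article.

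- **SAE rule** (Safety aspects and medical complications): "Any SAE (according to the study specific definition) reported by the subject or detected by the local investigator will be collected during the trial". The events are documented in case report forms, and the Ethics Committee is told within 24 hours of an SAE becoming known.
- **Safety parameters** (same section): "Safety parameters will comprise newly occurring mental diagnoses and all serious adverse events that are reported during and up to six months after treatment". On scope: "The recording of adverse events will be restricted to psychological conditions", that is, ICD-10 chapter F.
- **STPP contact** (Study design): "STPP entails five pre-treatment and up to 20 therapeutic sessions over a period of six months". The Intervention section adds that every session is videotaped and that each STPP patient is presented in supervision at three points.
- **TAU contact** (Study design): "Patients randomized to the TAU condition are not offered STPP, but obtain written information on local cancer counseling centers". Diagnostic findings also go to the general practitioner.
- **Assessments in both arms** (Abstract): pretreatment, 6 months and 12 months. Methods/design says the assessors are blind to the intervention.
- **Utilization record** (Study design): "Utilization of medical, psychotherapeutic and psychopharmacological treatment is documented throughout the study". The Discussion says it is assessed for all patients at both follow-ups.
- **Expected dropout** (Sample size calculation): "taking into account a slightly higher dropout rate of 30% in the TAU group vs. a 20% in STPP".

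**The concern.** A rule that waits for an event to be reported or noticed is only as sensitive as the contact behind it. Here that contact differs by design. The events in scope are psychiatric, and these are the kind most likely to be mentioned in a psychotherapy session. A psychiatric admission in the second month is likely to come to light earlier in STPP than in TAU, where the first stated study contact is the 6-month assessment.

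Two things are at stake. First, SAE counts set side by side would mix harm with ascertainment, and the likely direction is against STPP and towards understating the risk in TAU. Second, the 24-hour notice to the Ethics Committee starts when the event becomes known, so later discovery in TAU also delays oversight of the control group.

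**Working it through.** **1. Contacts after baseline.** The article's own maximum is reproduced: 5 pre-treatment + 20 therapeutic = 25 sessions, matching the 20 + 5 in the Abstract.

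| Period | STPP (maximum) | TAU |
|---|---|---|
| To month 6 | 25 sessions + 1 assessment = 26 | 1 assessment |
| Month 6 to 12 | 1 assessment | 1 assessment |
| Total | 27 | 2 |

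The imbalance belongs to the treatment phase. In the follow-up half-year the scheduled contacts are equal.

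**2. Loss of the shared contacts.** With 90 per arm, expected dropouts are 0.30 × 90 = 27 in TAU and 0.20 × 90 = 18 in STPP, a difference of 9. TAU therefore loses somewhat more of the only contacts it has.

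**3. What the symmetric sources cover.**

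| Source | Same in both arms? | Does it establish an SAE? |
|---|---|---|
| SCID-I by blinded assessors | Yes, at the same visits | No. It gives diagnoses, and so serves the other safety parameter. Seriousness rests on death, threat to life, hospitalization or disability. |
| Utilization record | Yes, all patients | It could reveal admissions, but no section links it to the SAE record. |
| Patient report or investigator detection | Same rule, unequal opportunity | Yes. It is the only stated route. |

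**4. Illustration of size.** The article gives neither an SAE risk nor a detection probability, so every value here is an assumption. With true risk *r* in both arms and detection probabilities d(STPP) and d(TAU):

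apparent ratio = [r × d(STPP)] / [r × d(TAU)] = d(STPP) / d(TAU)

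| d(STPP) | d(TAU) | Apparent ratio | Recorded per 90 at r = 5% | Recorded per 90 at r = 10% |
|---|---|---|---|---|
| 1.00 | 0.80 | 1.25 | 4.5 vs 3.6 | 9.0 vs 7.2 |
| 0.95 | 0.70 | 1.36 | 4.3 vs 3.2 | 8.6 vs 6.3 |
| 0.95 | 0.50 | 1.90 | 4.3 vs 2.3 | 8.6 vs 4.5 |

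The ratio only restates the assumed detection probabilities. The table shows direction and plausible range and estimates nothing.

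**5. Harm and detection combine.** If the true risk ratio were 2.0, with detection 0.95 and 0.70, the recorded ratio would be 2.0 × 0.95 / 0.70 = 2.71. An excess in STPP would thus be compatible with no harm or with real harm, and the counts alone could not tell the two apart.

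**The case against.** The strongest case on the other side has five parts.

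- **This is a condensed article.** Detection by the investigator may include asking at visits, and a full protocol, case report form or monitoring manual may fix the questions. That is possible and limits confidence. It does not remove the point, because the rule the article states is reactive and nothing in the article gives it equal sensitivity by arm.
- **No SAE test is planned.** Statistical analyses describes none. This stands: the concern is how counts by arm would be read, and no named analysis is invalid.
- **Symmetric safeguards exist.** They do, and the utilization record is well suited to catching a psychiatric admission in TAU. What is missing is its link to the SAE record.
- **Therapists are not SAE reporters.** They work in private practice and are not named as local investigators. The videotapes are described for rating adherence and competence. Study design only recommends the three supervision presentations. The path from session to SAE form is therefore a plausible inference, and one cannot say that an event in STPP becomes known at once.
- **TAU patients are not cut off.** They can report at any time, and patients in both arms are in active cancer treatment. That narrows the gap to an unknown degree.

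A reader might go further and infer that any difference between arms would be one of detection rather than harm. The article does not support this: unequal contact shows that the two cannot be separated, and leaves open which is at work. Nor does it support treating the 27 expected TAU dropouts as lacking a reporting route, since 18 are expected in STPP and patient report is not tied to visits.

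**Conclusion.** The point holds in limited form. As written, the SAE rule gives unequal opportunity for ascertainment during the six-month treatment phase. A difference in SAE counts could not be cleanly attributed to harm, and serious psychiatric events in TAU may be under-recorded or recorded late. The contact imbalance, up to 27 against 2, follows from the article's own figures. The resulting bias cannot be sized from them.

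The conclusion assumes that more contact raises the chance or speed of an SAE reaching the record, and that no scheduled inquiry exists in material not shown. It does not touch the primary endpoint or the comparison of new diagnoses by SCID-I. It is a change that should be made, held with medium confidence.

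**What to change.** Amend Safety aspects and medical complications as follows.

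1. Put the same fixed SAE questions to every patient in both arms at the existing 6- and 12-month assessments. Use a self-report form or someone other than the SCID rater, so that the answers do not unblind the rater.
2. Cross-check the SAE record in both arms against the utilization record already kept.
3. Apply the same follow-up inquiry to non-attenders in both arms. Visit questions cannot reach them, nor patients who have died.
4. Report all SAEs by arm, including deaths and events learned through therapy or supervision, with the route of detection flagged. Exclude no known SAE from the main safety report.
5. Add a comparison limited to events ascertained in the same way in both arms.

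Immediate reporting of events noticed between visits stays as it is. The cost is a short question set, one extra listing and the inquiry about non-attenders, with no extra visits. The main weakness is recall over up to six months, an interval that is the same in both arms.
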